The goal of this protocol paper is to describe a multi-site study comparing two school-based interventions, FYF-SB and ZOR via a cluster randomized controlled type 1 hybrid effectiveness-implementation trial [36] to determine which of the two interventions will best support autistic youth with anxiety in schools. Elementary and middle schools will be randomized to deliver either FYF-SB or ZOR to autistic students with interfering anxiety in small group format*.* Specific aims are as follows: 1) Compare the effectiveness of FYF-SB and ZOR on: (a) symptoms of anxiety (primary) and emotion dysregulation (co-primary) as rated by caregivers, students, teachers, and masked research staff; and (b) functional outcomes of priority to stakeholders, including school attendance, disciplinary action, and academic participation; 2) Compare the acceptability, appropriateness, and feasibility of FYF-SB and ZOR and a range of factors that contribute to the successful implementation of these two programs within schools; and 3) Examine autism severity and anxiety symptom severity as moderators of treatment response.

Results of this study will expand the intervention and implementation literature for autistic youth with co-occurring mental health conditions by providing evidence about the relative impact of two school-based mental health interventions on outcomes reported as meaningful by caregivers and school providers. The additional focus on evaluating factors that support the implementation of FYF-SB and ZOR will allow future studies to test targeted implementation strategies that support mental health programming uptake and implementation within public schools in order to meet the needs of autistic students and their families.

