### Student measures

#### Demographic Information

Caregivers will complete demographic information about their participating child and family. This includes the child’s age, race, ethnicity, grade and school placement, developmental and medical diagnoses, and school and community service history. Caregivers will also provide their own age, gender, race, ethnicity, highest educational obtainment, annual household income, household size, marital status, occupation, and the extent to which they experience psychosocial stressors such as food, housing, transportation, and healthcare related insecurities.

Primary outcome. screening for childhood anxiety and related emotional disorders – child/parent versions (SCARED) [41]*.* The SCARED is a 41-item inventory of statements that assesses five types of anxiety experienced by children and adolescents, to be completed separately by caregivers and students pre/post intervention and at 6 months follow-up. A total score, as well as cutoffs for specific domains of anxiety (e.g., social, generalized) are obtained. A total score of 25 or higher is clinically significant. Youth who obtain a score above the clinical cutoff for the total score or for 1 or more domains are eligible. The SCARED has been used in previous FYF-SB trials as well as in other studies with autistic children [24, 28]. Results from our previous research confirm the 41-item measure’s five-factor structure and suggest good sensitivity (0.71) and specificity (0.67) among parents of autistic youth [28].

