Co-primary outcome. pediatric anxiety rating scale-autism spectrum disorder (PARS-ASD) [43]. The PARS-ASD is a clinician-rated semi-structured interview assessing anxiety severity and impairment over the past week, modified for autistic youth ages 5 to 17 from the original Pediatric Anxiety Rating Scale (PARS) [44]. The PARS-ASD will be administered by an independent evaluator (IE) masked to condition. It includes a Symptom Checklist and five Severity Items. The Symptom Checklist covers social anxiety, separation anxiety, generalized anxiety, panic, specific phobia, and other anxiety symptoms. The severity of symptoms is examined by assessing the frequency and pervasiveness of anxiety, as well as the extent to which the child avoids anxiety provoking situations (e.g., behavioral manifestations of anxiety). Interference with family relationships within the home and interference with peer and adult relationships and/or performance outside of the home are also examined. Preliminary psychometrics were strong: internal consistency was 0.90; convergent validity was supported, as the PARS-ASD was strongly correlated with other parent-reported anxiety measures (*rs* = 0.62–0.68); divergent validity was also supported as the PARS-ASD had low correlations with parent ratings of social withdrawal, stereotyped movements, hyperactivity and repetitive behaviors [43].

Stakeholder identified outcomes. In previous research studies, stakeholder partners listed the following as meaningful treatment outcomes within schools: number of tardies, attendance, grades, number of elopements (leaving school area without permission), amount of classroom participation, number of expulsions and suspensions, number of visits to the principal and nurse, use of coping strategies, increase in self-advocacy, number of phone calls home, number of referrals to the social worker, increase in social initiations with others, and decrease in outbursts [26]. We will operationally define these outcomes and partner with school teams and school personnel to collect each of these outcomes on participating students from the academic year prior to study participation and the academic year in which students participated in FYF-SB or ZOR.

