### Analytic plan

Between-arm imbalance of baseline characteristics will be examined using* t* and chi-square tests and evaluated based on summary statistics. Intervention effect of FYF-SB as compared to ZOR will be assessed using Linear mixed effect model (LMM) for continuous outcomes and non-linear mixed effect model (NLMM) for categorical outcome such as school attendance. To account for the design effect of clustering trials, random school (cluster) effect will be in the models for outcome without repeated measures while appropriate covariance structure of LMM/NLMM accounting for both the design effect and the correlation of repeated measures will be used for outcome with repeated measures. Transformation of outcome (i.e., Square root or log) will be used if normality assumption is violated. Any imbalanced potential confounding variables will be adjusted for modeling. Primary analysis will be conducted on intent-to-treat basis (ITT). LMM and NLMM will be the primary method for dealing with missing values without data imputation since missing patterns would most likely be of the missing at random (MAR) pattern. The change score from baseline to the end of intervention is considered to the primary effectiveness endpoint. No type I error adjustment for multiple tests in a single model or multiple outcomes will be applied. *P* < 0.05 is deemed statistically significant. No interim analysis will be performed. To examine the robustness of primary analyses, sensitivity analyses will be conducted, including the same analyses among completers and analyses after missing data are imputed using Markov chain Monte Carlo method.

#### Aim 1

The SCARED and PRAS-ASD are the co-primary outcome variables. Both primary and secondary outcomes will be analyzed using the above discussed LMM/NLMM model with fixed effects consisting of time (i.e., baseline/end of treatment/6 months follow-up), comparator (FYF-SB or ZOR) and their interaction. Intervention effect of FYF-SB as compared to ZOR will be estimated by between-comparator difference in the change score of outcome measure from baseline (i.e., interaction) with 95% confidence interval and be tested statistically under the statistical model.

#### Aim 2

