### Sample size and power analysis

This study was primarily powered on detecting a between-comparator difference in the primary outcome (i.e., SCARED score) using ITT analysis. We expect the mean cluster size across the 100 schools to be 2 participants, ranging 2–5. Based on the FYF-SB RCT [28], estimates of ICC ranging from 0.001–0.15 were conservatively used in this power analysis. Our study will have 80% power at 5% significance level, with 100 participants per arm to detect a medium effect size (0.45 of Cohen’s D). Additionally, studies with autistic youth that each compared two active treatments further supported our anticipated effect size and power. Two studies reported significant treatment effects when comparing CBT adapted for autistic youth to other interventions (Standard CBT; Enhanced Standard Community Treatment) [57, 58]. The effect size when comparing these two active comparators was medium in size (ranging from 0.50- 0.63) [57, 58]. The effect sizes from these two studies are nearly equivalent to the effect size used for our current study, given that all are within the medium category according to effect size interpretation [59]. We will also have sufficient power to detect the medium effect size for the secondary outcomes.

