### Limitations

This is one of the first studies to directly compare the effectiveness and implementation outcomes of two school-based CBT programs for autistic students with anxiety. The cluster randomized trial is designed to use methods that are both rigorous (e.g., the use of masked evaluators for primary outcomes) yet that are also pragmatic within school settings. For example, rather than confirming autism diagnoses using resource-intensive, standardized assessments, this study will include students with an educational identification of autism or who have significantly elevated social communication differences as indicated by one or more screening tools. Thus, it is possible that students will be included who are not autistic. However, this more pragmatic inclusion criteria reduces measurement burden on students and caregivers and likely ensures a sample of students that is more reflective of students with social communication differences being services in schools. In addition to the use of pragmatic measures, this study intends to ensure that ZOR and FYF-SB training procedures are similar in length and format. However, it is possible that that attempting to standardize training and consultation masks meaningful differences in how these two programs are implemented in schools, and/or that some of the continued differences methods may impact how the two programs are implemented. Thus, there will be careful documentation of training procedures and the use of mixed methods to understand the role of training content and format on the ease of implementing the two programs.

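### The sections disagree on which outcomes are primary and no SCARED version is designated, yet each is tested at 0.05 with adjustment refused and no rule on whether one or all must succeed

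*Protocol article*

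**What the plan says.** The primary outcome is described in six places in the protocol article.

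- **Abstract, Methods:** child anxiety, from three sources (masked evaluator, caregiver, student).
- **Background, specific aims:** "symptoms of anxiety (primary) and emotion dysregulation (co-primary) as rated by caregivers, students, teachers, and masked research staff".
- **Student measures:** the SCARED is headed as the primary outcome and is "to be completed separately by caregivers and students pre/post intervention". The PARS-ASD is headed as co-primary: "The PARS-ASD will be administered by an independent evaluator (IE) masked to condition". The Emotion Dysregulation Inventory (EDI) entry carries no primary label.
- **Analytic plan, Aim 1:** "The SCARED and PRAS-ASD are the co-primary outcome variables" (the second name is a misprint for PARS-ASD).
- **Sample size and power analysis:** the study was mainly powered on "detecting a between-comparator difference in the primary outcome (i.e., SCARED score"), with no version named.
- **Limitations:** rigour is illustrated by "the use of masked evaluators for primary outcomes".

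On error control, the Analytic plan says "No type I error adjustment for multiple tests in a single model or multiple outcomes will be applied" and that a P value below "0.05 is deemed statistically significant". It fixes the primary time point as change from baseline to the end of the intervention.

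**The concern.** Two things combine. First, the reader cannot tell which outcomes are primary. Emotion dysregulation is co-primary in the aims and unlabelled in the measures and analysis, where the PARS-ASD takes that place. The SCARED is two scores from two informants, and nothing says whether the caregiver score, the student score or both are meant. Second, the plan refuses multiplicity adjustment across outcomes, exempts no primary outcome, and does not say whether one or all primaries must be significant.

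The trial is meant to show which of two programmes better supports these students, and school leaders are expected to act on the answer. If caregiver SCARED, student SCARED and masked PARS-ASD disagree, the text does not say which decides. Depending on the rule adopted later, either the 5% level or the 80% power may not describe the primary conclusion.

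**Working it through.** **Inputs from the protocol article.** Level 0.05 per test (taken as two-sided, in line with the 95% confidence interval in Aim 1); 100 students per arm; d = 0.45; stated power 80%; mean cluster size 2; ICC 0.001 to 0.15. No dropout rate is printed.

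**Inputs that are assumptions.** The article gives no correlation between these outcomes. A common correlation from 0 to 0.7 was tried. As rough proxies, 0.65 was used for the first pair of tests (the PARS-ASD text reports 0.62–0.68 with other parent-reported anxiety measures) and 0.34 for each with the third (the mean cross-informant value reported for the SDQ). These are correlations between scores, not between treatment-effect statistics.

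**1. The plan's own power figure.** Effective n per arm = 100 / (1 + (2 − 1) × ICC), which is 99.9 at ICC 0.001 and 87.0 at ICC 0.15. Power = Φ(0.45 / √(2 / n_eff) − 1.96).
- ICC 0.001: Φ(3.180 − 1.960) = 88.9%
- ICC 0.15: Φ(2.967 − 1.960) = 84.3%

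The stated 80% is therefore met as a floor for one outcome. An unstated 10% dropout would bring it to 80.4% at ICC 0.15. The single-outcome power figure is not the defect.

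**2. If any one significant primary counts.** With independent tests the chance of at least one false positive is 1 − 0.95^k. With correlated tests it was obtained by simulating multivariate normal statistics.

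| Primaries | Independent | Common r = 0.5 | Common r = 0.7 | Proxy r |
|---|---|---|---|---|
| 2 | 9.75% | 9.0% | 8.4% | 8.5% |
| 3 | 14.3% | 12.6% | 10.9% | 12.7% |
| 4 (with emotion dysregulation) | 18.5% | 15.6% | 13.1% | 15.6–16.5% |

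The proxy value for four assumes a correlation of 0.3 to 0.5 between the fourth outcome and the others.

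**3. If all primaries must be significant.** Type I error cannot exceed 5% whatever the correlation (about 0.9% for two outcomes at r = 0.5 when neither has an effect). Joint power, with the proxy correlations and d = 0.45 on every outcome:

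| Primaries | Printed inputs, no dropout (ICC 0.15 to 0.001) | Each test at exactly 80% |
|---|---|---|
| 2 | 76–83% | 71% |
| 3 | 67–76% | 60% |

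**4. If alpha is split.** Bonferroni power per outcome, no dropout, ICC 0.15 to 0.001: 76.6–82.6% for two outcomes (0.025 each) and 71.7–78.4% for three (0.0167 each). Holm is never less powerful than this.

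**The case against.** The strongest reply is that the operative text is narrower than it looks. Aim 1 and the measures section agree on two instruments, so emotion dysregulation as co-primary may be a stray label in one sentence. Co-primary is often taken to mean that all must succeed, in which case no adjustment is needed. And the SCARED version and the success rule are details a statistical analysis plan commonly supplies.

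Much of this stands, and it rules out several stronger readings.

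- A reader might infer four competing primaries with 16–18.5% error. The fourth rests on the aims sentence alone.
- A reader might infer that the trial has no 5% error rate at all. That holds only if any single win counts.
- A reader might infer that all-must-win power is well below 80%. For two outcomes on the printed inputs without dropout it straddles 80%; the lower figures need each test to have exactly 80%.
- A reader might see the sample size section as a further contradiction. Powering on one of two co-primaries does not redefine the primary set.
- A reader might conclude that the deciding result can be picked freely after the data are seen. The time point, the model and the Aim 1 instruments are fixed; what stays open is the SCARED version, the status of emotion dysregulation and the rule for combining results.

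What does not stand is the appeal to an unseen analysis plan. The co-primary labels conflict in the current text, and the refusal to adjust is a stated rule, not a gap. An analysis plan that controlled error across the primaries by adjustment would have to contradict it. Nor does the all-must-win defence settle the matter, since the article never states that rule.

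**Conclusion.** The point holds in conditional form. The co-primary label is inconsistent between the aims and the measures and analysis sections, the SCARED score that counts is not designated, and adjustment across outcomes is refused without a success rule. Under an any-win reading the false-positive chance is about 8–10% for the two instruments in Aim 1 and about 11–14% if both SCARED versions count; no correlation tried brings it back to 5%. Under an all-must-win reading the 5% level is safe and the cost falls on power, most clearly with three outcomes. The ranges rest on assumed correlations, an equal effect on each outcome and, unless stated otherwise, no dropout.

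A smaller matter belongs with the same revision: the Limitations remark on masking describes the PARS-ASD only. The SCARED, on which the trial is powered, is caregiver and student report.

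**What to change.** 1. Name the same primary outcomes in the Abstract, specific aims, Student measures, Aim 1 analysis and Sample size sections. State which SCARED version is meant and whether emotion dysregulation is primary or secondary.
2. Control error across the named primaries by one stated rule:
   - a fixed sequence at two-sided 0.05, for example the designated and powered SCARED version first, then the PARS-ASD, with confirmatory claims stopping at the first non-significant test (the order is the sponsor's choice);
   - Holm across the primaries; or
   - an explicit rule that all must be significant.
3. Limit the no-adjustment sentence to secondary outcomes.
4. Restate power under the chosen rule.
5. Reword the Limitations remark so that masked evaluation is claimed for the PARS-ASD only.

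**Cost.** These are changes of wording, with no new data. Enrolment has begun, so they should be settled before outcomes are examined. A fixed sequence keeps the stated power for the first outcome, but later outcomes can be claimed only if earlier ones succeed. For two outcomes, Holm has at least the Bonferroni power of about 77–83% each without dropout. An all-must-win rule carries the joint power shown above.

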Quantitative data will be analyzed in the same fashion as for the outcome without repeated measures in Aim 1. Consistent with CORE-Q reporting guidelines [54], all interviews will be audio-recorded, and transcribed verbatim. ​​Exit interview data will be formally analyzed using conventional content analysis [55, 56]. This form of analysis is commonly used in studies with the aim of describing a phenomenon at a level that closely reflects the transcript content. In the case of Aim 2 data, the content analysis will be used to closely describe stakeholder perspectives of the feasibility (i.e., ease of use), acceptability, and appropriateness of FYF-SB or ZOR, as well as the infrastructure necessary to implement and sustain these programs. All coding will be facilitated by MAXQDA software. Additionally, all qualitative results will be member checked with our stakeholder advisory board members prior to synthesis into various products.

#### Aim 3

To explore the impact of baseline symptoms and other demographic variables on the intervention effect, we will include similar models to those being tested in Aim 1, with the use of an interaction term (i.e., intervention x moderator x time interaction) in addition to related two-way interaction terms. Candidate moderators, including age, will be examined. If an interaction results in significance, we will further test treatment effects within subgroups analogous to hypotheses in Aim 1. Similar analysis will also be conducted with the outcome dichotomized as responder and non-responder using clinical criteria.

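### When the Aim 3 moderator is the outcome's own baseline score, the three-visit model fits the baseline rows exactly, so the fit is singular or the standard error of the moderation test is off

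*Protocol article*

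**What the plan says.** All places are in the protocol article.

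- **Background, specific aims.** The third aim is to "Examine autism severity and anxiety symptom severity as moderators of treatment response".
- **Analytic plan, Aim 3.** The purpose is to "explore the impact of baseline symptoms and other demographic variables on the intervention effect", so the severity moderator is a baseline value. The moderation terms are specified "with the use of an interaction term (i.e., intervention x moderator x time interaction) in addition to related two-way interaction terms". The moderator-by-time term is therefore included. For the underlying model the authors write: "we will include similar models to those being tested in Aim 1".
- **Analytic plan, Aim 1.** The model has "fixed effects consisting of time (i.e., baseline/end of treatment/6 months follow-up), comparator (FYF-SB or ZOR) and their interaction". Baseline is one of three response times. On outcomes: "The SCARED and PRAS-ASD are the co-primary outcome variables" (the second is the PARS-ASD). Both measure anxiety.
- **Analytic plan, opening paragraph.** For repeated measures the plan promises an "appropriate covariance structure of LMM/NLMM accounting for both the design effect and the correlation of repeated measures" and names no structure.
- **Consequence of a positive test (Aim 3).** "If an interaction results in significance, we will further test treatment effects within subgroups analogous to hypotheses in Aim 1".

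The article names neither the scale nor the informant for the anxiety moderator, and does not say whether it is continuous or categorised.

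**The concern.** Read together, these sections allow one score to stand on both sides of the model. The moderator and its interaction with time give the score its own slope at each visit. At the baseline visit, if moderator and outcome are the same score, that slope is 1, every other baseline term is 0, and the residual is 0 for every student.

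The moderation contrast is the moderator-by-arm difference in change from baseline. Its standard error comes from the modelled residual covariance across visits. A visit with no residual variance either makes that covariance singular or, where variances are pooled over visits, mixes a zero with the real later variances.

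At stake is the p-value for one of the two moderators named in the aims. A significant result leads to subgroup tests, and the plan applies no multiplicity adjustment.

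**Working it through.** The plan gives no figure for Aim 3, so there is none to reproduce. The stated power concerns the primary comparison and does not enter here.

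**Inputs.** From the article: three visits, baseline among the responses, and the three-way term with its two-way terms. Assumed: complete data, equal residual variance s² at post-treatment and 6 months given baseline, and r, the correlation of those two residuals. The documents give none of these, so r is shown as a range.

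**Step 1: residual covariance.** With the outcome's own baseline as moderator, the variances at the three visits are 0, s² and s². The covariances are 0, 0 and r·s². The 3 x 3 matrix has rank 2. An unstructured covariance is therefore singular, and any structure with a separate baseline variance drives that variance to zero.

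**Step 2: pooled structure.** Compound symmetry (random intercept) uses one variance and one covariance:

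- variance = (0 + s² + s²)/3 = 2s²/3
- covariance = (0 + 0 + r·s²)/3 = r·s²/3
- modelled variance of change = 2 x (2s²/3 - r·s²/3) = s²(4 - 2r)/3
- true variance of change given baseline = s²

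The ratio of modelled to true standard error is k = sqrt((4 - 2r)/3). The actual size of a two-sided 5% test is 2 x [1 - Φ(1.96k)].

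| r | k | Standard error | Actual size |
|---|---|---|---|
| 0.3 | sqrt(3.4/3) = 1.065 | about 7% too large | 3.7% |
| 0.5 | sqrt(3.0/3) = 1.000 | correct | 5.0% |
| 0.7 | sqrt(2.6/3) = 0.931 | about 7% too small | 6.8% |
| 0.8 | sqrt(2.4/3) = 0.894 | about 11% too small | 8.0% |

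**Step 3: simulation.** 100 schools of 2 students, 4000 trials per setting, no true moderation. Assumed: ICC 0.10 in the baseline score and baseline-to-later correlation 0.6.

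- The residual covariance had rank 2 in every setting.
- The compound-symmetric test rejected in 3.1% of trials at r = 0.2, 4.3% at 0.5, 6.4% at 0.65 and 8.7% at 0.8.
- A post-treatment regression on arm, baseline score and their product held its size at 4.6% to 5.7% for every r.

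**Step 4: fitted mixed models.** In single simulated data sets the random-intercept and post-treatment-regression point estimates agreed. The standard errors were 0.126 against 0.107 at r = 0, and 0.113 against 0.128 at r = 0.8. Adding a school random effect barely changed the mixed-model values (0.125 and 0.113) and brought boundary and convergence warnings.

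**Step 5: where it stops.** With a moderator from another scale (assumed correlation 0.65 with the outcome's baseline), or with a dichotomised baseline score, the covariance had full rank and an unstructured fit held its size (4.8% to 5.5%). Compound symmetry still ran from 3.7% to 8.7%, but that is ordinary covariance misspecification, not self-prediction.

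**The case against.** The strongest reply is that the article does not commit to the failing model.

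- **Scale and form of the moderator.** The trial has parent and child SCARED, PARS-ASD and a teacher anxiety scale, and the planned subgroup tests are compatible with a categorised moderator. A different scale or a split score avoids exact self-prediction. This stands, and limits the point to the same-scale, same-informant, continuous case.
- **Latitude in the wording.** Aim 3 promises models similar to those of Aim 1, not identical ones, and detail may sit in an analysis plan that is not shown. This stands in part. But the article does state the response times and the interaction terms, and nothing in it takes baseline out of the response for Aim 3. The point is about that stated combination, not about missing detail.
- **Covariance left open.** The promise of an appropriate structure might be thought to cover the case. It does not: separate visit variances are singular and pooled ones misstate the standard error. A singular fit would probably be noticed; a random-intercept fit could run without showing that its standard error is off.
- **Low consequence.** The aim is exploratory, the point estimate is sound, and the direction of the error depends on an unknown correlation. This stands, and keeps the point minor.

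A reader might infer that every Aim 3 test of anxiety severity predicts baseline from itself, or that the tests are generally too liberal. The documents support neither: the moderator's scale is not named, and the error reverses sign at r = 0.5.

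**Conclusion.** The point holds conditionally and is minor. If the moderator is the continuous baseline score of the same scale and informant as the outcome, the three-visit model fits the baseline rows exactly. A covariance with its own baseline variance is then singular. A pooled one gives a standard error between about 7% too large and 11% too small for r between 0.3 and 0.8, with an actual test size of about 4% to 8%. These figures rest on complete data, equal residual variance at the two later visits, and a compound-symmetric or random-intercept fit, which the article allows but does not name.

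It would be wrong to read this as bias in the moderation estimate or as a fault in the primary comparison. With complete data the estimate is unchanged, and the Aim 1 model contains no moderator. Age, autism severity and other moderators that are not the outcome's own baseline are free of the self-prediction.

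**What to change.** Add one sentence to Aim 3. Where the moderator is the outcome's own baseline score:

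- take only the post-treatment and 6-month scores as responses;
- fit the full factorial of baseline score, arm and time, with all main effects and all two-way terms, including arm by time and baseline by time;
- use an unstructured two-visit covariance and the same allowance for school;
- test moderation at post-treatment by the baseline-by-arm contrast at that visit.

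Keep the three-visit model for all other moderators.

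The two-way terms must not be dropped. In a simulation with no true moderation (200 students, residual correlation 0.5, baseline slope changing from 0.60 to 0.45 between visits), omitting arm by time and baseline by time made the three-way test reject 48% of the time, far worse than the problem being repaired.

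The cost is the added sentence and a separate model for this one moderator. No information on moderation is lost with complete data, because baseline rows that are fitted exactly carry none.
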